### Role of Health Care Personnel

Pregnant women attending the pregnancy care services of the APSS will be recruited between the 24th and 26th week of gestation. To identify women potentially eligible to participate in the study and collect informed consents and initial sociodemographic data, the involvement of some midwives or doctors belonging to the hospital and territorial service of the APSS is planned.

### Study Outcomes

#### Primary Outcome

The primary outcomes are UX and UE. They will be assessed using 2 questionnaires, namely, the Mobile Application Rating Scale (MARS) [19] and the User Engagement Scale–Short Form (UES-SF) [20], which will be administered at different time slots throughout the study, in particular, at the end of week 4 and at the end of the study (ie, week 8).

The end points that will be measured are as follows: a score of the individual items of the questionnaires (MARS and UES-SF); the average score of the questionnaires; and the difference between the average score values of the individual questionnaires at different survey times.

The evaluation of the experience of using the app and the virtual coach (Maia) and the use of the intervention itself will also be assessed through semistructured interviews, conducted 2 months after childbirth. In this case, qualitative data will be collected to enrich the information related to the primary outcome.

#### Secondary Outcome

The variable expressing the “psychological well-being” outcome will be assessed by administering self-report questionnaires at the beginning (ie, week 1) and end (ie, week 8) of the psychoeducational course (refer to Table 1 for a detailed overview of the questionnaire adopted). The end points that will be measured are as follows: a score of the individual items of the questionnaires; the average score of the questionnaires; and the difference between the average score values of the individual questionnaires in the 2 survey times.

**Table 1 table1:** Summary of the questionnaires administered and their timing.

At the beginning of the study (week 1)	At the end of week 4	At the end of the study (week 8)	Follow-up (2 months after birth)
SF-12 v1^a^	N/A^b^	SF-12 v1	Qualitative interview
DASS-21^c^	N/A	DASS-21	N/A
IES-R^d^	N/A	IES-R	N/A
FFMQ^e^	N/A	FFMQ	N/A
PANAS-SF^f^	N/A	PANAS-SF	N/A
ERQ^g^	N/A	ERQ	N/A
N/A	MARS^h^	MARS	N/A
N/A	UES-SF^i^	UES-SF	N/A

^a^SF-12 v1: Short Form–12 Health Survey Version 1.

^b^N/A: not applicable.

^c^DASS−21: Depression Anxiety Stress Scales–21.

^d^IES-R: Impact Event Scale–Revised.

^e^FFMQ: Five Facet Mindfulness Questionnaire.

^f^PANAS-SF: Positive and Negative Affect Schedule–Short Form.

^g^ERQ: Emotion Regulation Questionnaire.

^h^MARS: Mobile Application Rating Scale.

^i^UES-SF: User Engagement Scale–Short Form.

The mindfulness-based childbirth and parenting protocol is aimed at creating a connection between expectant mothers and their bodies and fetuses. The literature highlights the growing interest in mindfulness-based interventions [21] due to their consistent effects, including reduced depressive [22], anxiety [23], and stress symptoms [24] as well as enhanced emotional regulation [25] and sleep quality [26].

Therefore, we intend to incorporate variables such as maternal stress levels, frequency of mindfulness practice, and gestational age as predictors. Particularly, we will explore stress and anxiety (Impact Event Scale–Revised and Short Form–12 Health Survey, Version 1), depression (Depression Anxiety Stress Scales–21), emotion regulation (Positive and Negative Affect Schedule–Short-Form and Emotion Regulation Questionnaire), and mindfulness level (Five Facet Mindfulness Questionnaire).

These confounding variables are pivotal as they could impact both the independent variables and outcomes, ensuring a comprehensive understanding of the association between mindfulness and maternal health outcomes. By addressing these factors, we aim to deliver a more robust analysis of the efficacy of mindfulness interventions during pregnancy.

### Data Collection

The midwives will collect the sociodemographic data at the time of enrollment using a prestructured form. A unique alphanumeric code will be used to link the different pieces of information with the project’s participants. The sociodemographic data collection form and the data collected during the study will be kept separately. In addition, data will be pseudonymized to ensure confidentiality.

The parameters requested from the women will be (1) age, (2) week of pregnancy, (3) weight and height, (4) socioeconomic level, (5) educational level, (6) occupation, (7) marital status, (8) number of pregnancies, and (9) current or previous experience of psychological support (to investigate and describe the prevalence of women who have requested support to care for their psychological well-being).

The participants will also be asked if they would like to participate in a qualitative interview 2 months after delivery. In case of positive feedback, their telephone number will be collected to facilitate future contact and follow-up interviews.

To properly assess participants’ experience during the psychoeducational pathway, some questionnaires were adopted and delivered at the beginning, during, and at the end of the interaction with Maia (Table 1).

Specifically, 8 questionnaires will be administered at the beginning and the end of the psychoeducational intervention. Two questionnaires will be delivered during the psychoeducational pathway to assess the usability and engagement of the woman with the app and Maia. Specifically, the usability questionnaires will be administered at the end of week 4 and week 8 (ie, the end of the study).

A detailed description of each instrument that will be administered is presented in the following paragraphs.

Short Form–12 Health Survey Version 1 [27] is a self-report questionnaire characterized by 12 items assessed on different scales (Likert and dichotomous). The questionnaire investigates the QoL in 8 health dimensions to assess physical and mental health. Domains related to physical health include (1) general health, (2) physical functioning, (3) physical role, and (4) body pain. The mental health scales include (1) vitality, (2) social functioning, (3) emotional role, and (4) mental health. The questionnaire was translated and culturally adapted into various European languages and countries, including Italy, as part of the International Quality of Life Assessment project.

The Depression Anxiety Stress Scales–21 [28] is a self-report questionnaire consisting of 21 items based on a 4-point Likert scale, ranging from 0 (it never happened to me) to 3 (it almost always happened to me). This questionnaire is characterized by 3 scales investigating symptoms of anxiety, depression, and stress, including a total distress scale. Higher scores correspond to a higher level of distress. This scale was translated into Italian and validated in an Italian context [28]. The total scale found very good internal reliability (α=.90).

The Impact Event Scale–Revised [29] is a self-report questionnaire consisting of 22 items rated on a 5-point Likert scale, ranging from 0 (not at all) to 4 (extremely). This questionnaire assesses the impact of events that may be perceived as stressful through three scales: (1) intrusion, (2) avoidance, and (3) hyperarousal. This questionnaire will be administered in this research project to consider the investigated data net of the participant’s pregnancy situation, eliminating potential external stressors (eg, COVID-19). The questionnaire was translated and validated in an Italian context [29]. The 3 scales show good internal reliability: α=.78 for intrusion; α=.72 for avoidance; and α=.83 for hyperarousal.

The Five Facet Mindfulness Questionnaire [30] is a self-report questionnaire consisting of 39 items rated on a 5-point Likert scale, ranging from 1 (never or very rarely true) to 4 (very often or always true). The questionnaire assesses the tendency to be attentive in daily life using five scales: (1) observe, (2) describe, (3) act with awareness, (4) do not judge, and (5) do not react. Higher scores indicate greater awareness. The questionnaire was translated and validated in an Italian context [31]. The Cronbach α values were .74 for observation, .92 for description, .85 for acting with awareness, .91 for nonjudgment, .79 for nonreactivity, and .84 for total score, indicating good reliability.

The Positive and Negative Affect Schedule–Short Form [32] is one of the most widely used instruments to assess positive and negative affective states. It measures 2 distinct and independent dimensions: positive affection (PA) and negative affection (NA). The questionnaire consists of 20 adjectives, 10 for the PA subscale and 10 for the NA subscale. The PA subscale reflects the degree to which a person feels enthusiastic, active, and determined; the NA subscale refers to general unpleasant states, such as anger, guilt, and fear. The participant is asked to rate how they generally feel in the manner described by the adjective, responding on a 5-point Likert scale (1=not at all to 5=very much). The instrument has excellent psychometric properties: the internal consistency coefficient of the PA subscale ranges from 0.86 to 0.90 and that of the NA subscale ranges from 0.84 to 0.87. Furthermore, the test has good convergent and divergent validity. The 2 subscales show a low correlation (−0.12 to −0.23), and this characteristic aligns with the theory that the 2 factors, PA and NA, are independent. The questionnaire has been translated into many languages; the Italian version was validated by Terracciano et al [33] on a sample of 600 participants and replicated the psychometric characteristics of the original study.

The Emotion Regulation Questionnaire [34] is a 10-item scale designed to measure the tendency to use 2 emotional regulation strategies, that is, cognitive reappraisal and expressive suppression. Respondents answer each item on a 7-point Likert-type scale, ranging from 1 (strongly disagree) to 7 (strongly agree). Balzarotti et al [35] translated and validated the questionnaire in Italian, showing good psychometric characteristics. In this study, Cronbach α was .81 for cognitive reappraisal and .84 for expressive suppression.

The MARS [36] is characterized by 23 items rated on a 5-point Likert scale, ranging from 1 (poor) to 5 (excellent), which assesses the quality of the app and its functionalities (eg, virtual coach) on 4 dimensions of objective quality: engagement (5 items), functionality (4 items), esthetics (3 items), and information (7 items), as well as a final scale assessing subjective quality (4 items). The average of the scores of the individual items will be calculated to obtain an average quality score for each dimension investigated; subsequently, the average of the scores of the 4 objective quality dimensions will be calculated to obtain a total MARS score. The questionnaire also includes an “application-specific” section (6 items) to assess the potential impact of a particular app on the users’ knowledge, intentions, and so on. The total and subscale scores of the MARS have very high Cronbach α coefficients (.90 and .80-.89, respectively). The scale has been validated in an Italian context [36]. For this study, only the subscales “information,” “subjective quality of the app,” and “app-specific” will be considered for 17 items.

The UES-SF [37] is a short self-report questionnaire to assess UE with a digital solution. This measure includes 12 items based on a 5-point Likert scale, ranging from 1 (strongly disagree) to 5 (strongly agree). The questionnaire consists of four factors: (1) focused attention, which indicates the feeling of being immersed in the interaction; (2) perceived usability, which is the negative effect experienced due to the interaction and the effort expended; (3) esthetic attractiveness, which represents the graphical and visual appeal to a digital solution; and (4) the reinforcement factor (ie, reward). The reinforcement factor is a single factor that includes duration, which evaluates the overall success of the interaction; novelty, which examines the general interest related to the interaction with a digital solution; and, finally, the perceived engagement factor, which evaluates the overall enjoyment of the interaction. This questionnaire had not been translated into Italian and was therefore translated through the back translation procedure. The 4 scales show good internal reliability: ω=0.82 for focused attention, ω=0.86 for perceived usability, ω=0.84 for esthetic attraction, and ω=0.81 for reinforcement.

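### The only overall MARS score the protocol defines needs four dimensions, but the study keeps one of them, so the MARS average among the primary end points has no workable definition

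*Protocol article*

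**What the plan says.** The Primary Outcome section states: "The primary outcomes are UX and UE". It assigns two questionnaires to them, MARS and the User Engagement Scale–Short Form (UES-SF). The end points are the individual item scores and then "the average score of the questionnaires; and the difference between the average score values of the individual questionnaires at different survey times". On timing, Data Collection says that "the usability questionnaires will be administered at the end of week 4 and week 8 (ie, the end of the study").

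The MARS paragraph under Data Collection gives the structure of the scale: "engagement (5 items), functionality (4 items), esthetics (3 items), and information (7 items), as well as a final scale assessing subjective quality (4 items"). It adds a separate part: "The questionnaire also includes an “application-specific” section (6 items"). Scoring has two steps. Items are averaged within each dimension, and then "the average of the scores of the 4 objective quality dimensions will be calculated to obtain a total MARS score". The paragraph quotes a Cronbach α of .90 for the total and .80 to .89 for the subscales. It closes with the restriction: "For this study, only the subscales “information,” “subjective quality of the app,” and “app-specific” will be considered for 17 items".

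**The concern.** The scoring rule and the item set stand in one paragraph and do not fit together. The rule needs engagement, functionality, esthetics and information. The restriction keeps information and adds two parts that the rule does not use. The paragraph describes subjective quality as a final scale beside the objective ones, and the app-specific items as an additional section.

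This matters because MARS is one of only two questionnaires for the primary outcomes, and two of the three listed end points rest on an average questionnaire score. The MARS paragraph is the only place that says how an overall MARS score is formed. If that rule cannot be applied and nothing replaces it, the analyst has to choose a summary, possibly after seeing the data. The candidates are the information mean alone, the mean of all 17 items, and the mean of the three subscale means. These can give noticeably different results, and none of them is the score the paragraph defines.

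**Working it through.** **Inputs** (all from the MARS paragraph under Data Collection): engagement 5 items, functionality 4, esthetics 3, information 7, subjective quality 4, app-specific 6. Items are rated 1 to 5.

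**1. Reproduce the protocol's item counts.**
- Core scale: 5 + 4 + 3 + 7 + 4 = 23, as stated.
- Retained set: information 7 + subjective quality 4 + app-specific 6 = 17, as stated.

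Both counts agree, so the restriction means what it says and is unlikely to be a slip in the subscale names.

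**2. Compare the retained set with what the total needs.**

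| Part | Items | Enters the total? | Retained? |
|---|---|---|---|
| Engagement | 5 | yes | no |
| Functionality | 4 | yes | no |
| Esthetics | 3 | yes | no |
| Information | 7 | yes | yes |
| Subjective quality | 4 | no | yes |
| App-specific | 6 | no | yes |

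- Objective items required: 5 + 4 + 3 + 7 = 19.
- Retained: 7 of 19 (37%), or 1 of 4 dimensions.
- Missing: 5 + 4 + 3 = 12 items, or 3 of 4 dimensions.
- Retained items outside the total: 4 + 6 = 10 of 17 (59%).

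The four full objective dimensions need 19 items, so no choice of complete subscales adding up to 17 items could contain all four.

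**3. Is the total recoverable from what is retained?** Write it as T = (E + F + A + I)/4, where E, F, A and I are the four dimension means. With I known and E, F and A each free between 1 and 5, T lies between (I + 3)/4 and (I + 15)/4.
- For I = 4.0: from (4 + 3)/4 = 1.75 to (4 + 15)/4 = 4.75.
- The interval is 12/4 = 3 points wide whatever I is, on a scale that spans 4 points.

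T is therefore not identified.

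**4. How far could substitute summaries differ?** This is an illustration with assumed means, which are not in the protocol: information 4.5, subjective quality 3.0, app-specific 3.5.
- Information only: 4.50.
- Mean of 17 items: (7 × 4.5 + 4 × 3.0 + 6 × 3.5)/17 = (31.5 + 12 + 21)/17 = 64.5/17 = 3.79.
- Mean of three subscale means: (4.5 + 3.0 + 3.5)/3 = 11/3 = 3.67.
- Spread: 4.50 − 3.67 = 0.83 points, due only to an unstated scoring choice. If the three subscale means were equal, the spread would be zero.

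**The case against.** The best defence is that the Primary Outcome section never names a MARS total. It speaks of item scores, average scores and differences, and the first scoring step, a mean for each dimension, works for the retained subscales. The study is a single-arm proof of concept with mainly descriptive analysis, and no success threshold or sample-size figure rests on the MARS total. All of this stands, and it limits the size of the problem. It does not remove it. The total is still announced as something that will be calculated, and no other overall MARS average is defined.

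Several stronger readings are tempting but not supported.
- *The missing dimensions will not be administered.* The protocol says only that three subscales will be considered. A 17-item form is the natural inference, but not a stated fact. The total is ruled out either way if only those subscales are used.
- *The primary outcome is lost, or user experience is not measured.* MARS item scores and subscale means remain, and nothing in the protocol places information or subjective quality outside user experience.
- *Usability and engagement go unmeasured.* Data Collection says the two questionnaires serve "to assess the usability and engagement of the woman with the app and Maia". The UES-SF, also given at weeks 4 and 8, covers perceived usability, esthetic attractiveness, focused attention and perceived engagement. Activity logs and interviews add to this. Leaving out overlapping MARS scales is a defensible way to limit burden.
- *The protocol claims a reliability of .90 for its selection.* It quotes that value as a property of the published instrument's total. The caution is only against carrying it over.

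Nor is this a detail that an article may leave to a fuller document. The article states both the rule and the restriction, and a fuller plan could not follow both.

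**Conclusion.** The point holds as a contradiction within one paragraph that reaches two of the three listed primary end points for one of the two instruments. The MARS total as defined cannot be computed, because three of its four components (12 of 19 objective items) are excluded. The average MARS score and its week 4 to week 8 difference therefore have no valid overall definition.

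The conclusion rests on the stated subscale names and item counts, which agree with each other, and on reading the restriction as governing which items are used. It does not depend on whether the other items are collected. It does not extend to the item scores, the three subscale means or the UES-SF, and it does not show that the choice of subscales was wrong. The score of 4.0 in step 3 and the subscale means in step 4 are illustrations, not expected values.

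**What to change.** In the MARS paragraph, delete the sentence that forms a total from the four objective dimensions and state that no MARS total is calculated. In the Primary Outcome section, name the MARS end points as the means of the three retained subscales (information, subjective quality, app-specific), each reported separately at week 4 and week 8, with the difference between the two time points. Item scores can stay as listed. Do not apply the total-score α of .90 to the 17-item selection, and do not compare any average of it with standard MARS totals.

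The cost is a few lines of wording, with no new data, visits or items. The change should be made before MARS scores are examined, since afterwards it becomes a post hoc scoring choice.

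Keeping all four objective dimensions would also restore the total, at the price of 12 more items at each of two time points. Adding only the four functionality items is optional and not part of the correction: it would bring the set to 2 of 4 dimensions, and the total would still not be computable.

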### Qualitative Interview

The interviews will be conducted by a psychologist from FBK. Interviews are structured with ad hoc items to purposively capture specific characteristics of the study and participants’ experiences. During the qualitative interview, the participants will also be asked if someone supported them during the course, whether it was helpful, and how easy it was to involve another person in some of the exercises. This will allow them to reason, in terms of experience, about whether to involve their partner or a trusted person in a more structured way in the intervention itself. Interviews will be conducted 2 months after the birth; will last approximately 20 minutes; and, subject to the woman’s consent, will be audio recorded to allow subsequent analysis.

The platform adopted for the intervention allows for the recording of activity logs, enabling proper mapping of the participants’ actions and experiences. This covers a range of logs, assessing whether the participant is properly exposed to the intervention protocol while recording use patterns (eg, session execution time, number of accesses, and use patterns of different features). Any missed sessions or interruptions will be considered as variables. These data will be correlated with acceptability scores during the analysis phase. In case a participant does not complete the activities and misses filling in specific questionnaires (leading to missing data), specific pieces of information on their experiences and platform use will be collected during the scheduled postintervention interview sessions.

### Privacy and Data Protection

Concerning data protection, a privacy policy will be formulated pursuant to articles 13 and 14 of the regulation EU 2016/679 of the General Data Protection Regulation, explaining the purposes and legal grounds of the data processing, how the personal data will be collected, the data collection categories, and how data will be managed, including the data retention period, the obligations of the data controllers, and the rights of the participants. The data controllers are APSS and FBK. Personal data are processed for specific research purposes within the scope of public interest tasks of the data controllers. Informed, voluntary, and explicit consent regarding the processing of particular categories of personal data (ie, data concerning health and data on self-reported behavioral habits in the area of lifestyle health) will be collected. Moreover, a specific consent will be asked on the possibility to contact the participant via telephone to carry out the interviews for the research.

All data collected will be kept confidential, managed by authorized persons, and data necessary for evaluating the study objectives will be pseudoanonymized before processing. Therefore, data are pseudonymized and not anonymized.

Copies of the information on the study and the privacy policy will be issued to the participants and made available permanently in a dedicated section of the app.

The study manager undertakes the responsibility to produce a report on the research and to ensure that the data are reported responsibly and consistently. Personal data will neither be disclosed nor disseminated, except in anonymized or aggregated form for publishing purposes. The publication of data resulting from this study will take place independently of the results obtained. The transmission or dissemination of the data, by means of scientific publications or presentations at congresses, conferences, and seminars, will take place exclusively in anonymous form using only aggregated data that prevent any identification of the participants, even indirectly. This sharing is expected to happen within 1 year after the conclusion of the study.

As the participants use the TreC Mamma app, they will be able to give their consent to be contacted for other research initiatives, including initiatives aimed at the continuous improvement of the platform and the acceptability and usability of the app, the collection of data in aggregated form for epidemiological purposes, and promoting specific projects in the social health care field. For all research activities, as the consent should be specific, dedicated information will be provided, and an ad hoc explicit consent will be requested. Using an eHealth mobile app as a “technological intermediary” to enroll users in medical research projects creates an “alliance with the citizens” of the PAT for the proactive use of personal data in scientific studies.

